# Implementation of a Bundle of Care in Colorectal Surgery to Reduce Surgical Site Infections Successfully at Cantonal Hospital Lucerne: Study Protocol for a Prospective Observational Study

**DOI:** 10.29337/ijsp.150

**Published:** 2021-09-23

**Keywords:** colorectal surgery, bundle of care, surgical site infection

## Abstract

**Background::**

Surgical site infections (SSIs) remain a relevant problem in colorectal surgery. The aim of this study is to implement a bundle of care in order to reduce SSIs in colorectal surgery.

**Methods::**

All patients undergoing colorectal surgery between October 2018 and December 2021 will be included in a prospective observational study. Since our colorectal bundle has been established gradually, patients will be grouped in a pre-implementation (2018–2019), implementation (2019–2020) and post implementation phase (2021), in order to assess the effectiveness of the actions undertaken. Primary endpoint of this study will be surgical site infection (SSI) rate, while secondary endpoints encompass potential risk factors for SSIs. We assume that obesity, age, diabetes, alcoholism and smoking may lead to a higher risk for SSIs.

**Discussion::**

This study aims to determine whether the colorectal bundle designed and implemented at Cantonal Hospital Lucerne, will lead to a significant reduction of SSIs. The impact of potential risk factors for SSIs will additionally be evaluated.

**Trial registration::**

ClinicalTrials.gov, ID: NCT04677686. Registered retrospectively 18 December 2020.

**Highlights::**

## Background

SSIs are a common problem in the healthcare system [1]. They lead to an increased mortality and morbidity rate. Apart from the negative impact on patients, SSIs cause high healthcare costs due to prolonged hospital stay and readmission of patients. Colorectal surgery, in particular, is associated with a high infection rate ranging from 15% to 30% [2,3].

In order to understand the causes of SSIs, risk factors have to be evaluated. Intrinsic and extrinsic factors have previously been defined [4]. Intrinsic risk factors are patient-associated and can be subclassified in modifiable and non-modifiable features. Modifiable intrinsic risk factors include diabetes, alcoholism, smoking status, obesity and preoperative albumin level. Examples of non-modifiable risk factors include age and recent radiotherapy. Extrinsic risk factors are procedure-related and involve emergency surgeries or facility risk factors. There are several strategies to prevent SSIs. The biggest impact has been found in the combination of different measures into a bundle of care [5,2,6].

The Cantonal Hospital Lucerne (LUKS) is an 870-bed public acute care teaching hospital serving a population of about 500.000 people in central Switzerland. From October 2016 till September 2017 the rate of SSIs in colorectal surgery in LUKS was 18.1% whereas the average rate of SSIs in Switzerland was 13.7% during the same period of time [7]. These nationwide data were collected and analyzed by Swissnoso, an organization monitoring SSIs cross-disciplinary.

In order to reduce the SSIs at LUKS, we created a colorectal bundle containing 9 measures. These measures were based on a literature research and selected in cooperation with the Department of Hospital Infection Control.

## Methods and design

### Study design

This prospective observational monocentric study will commence at LUKS, a large non-university hospital in Switzerland. A total of 150 patients will be included between January 2021 and December 2021. Ethical approval has been obtained from the responsible Swiss Ethics Committee (EKNZ) with the project ID: 2020–00051. The study is registered at ClinicalTrials.gov with the number NCT04677686.

### Patient population

All patients undergoing colorectal surgery from January 2021 until December 2021, fulfilling the inclusion criteria and having signed an informed consent form will be included in the study. According to our annual case load, we expect to enroll about 150 patients in the study. The data of the patients which are prospectively included in this study will be compared with the data analyzed by Swissnoso (October 2017–September 2018 and October 2018–September 2019). From 2017–2018 153 patients were included and 31 infections were detected (5 superficial, 8 deep and 18 involving the abdominal cavity).

From 2018–2019 after partial implementation of the colorectal bundle actions 126 were included and 15 infections occurred (2 superficial, 4 deep and 9 involving the abdominal cavity). Concerning the three time periods, data acquisition is retrospective for the first two periods and prospective for the final period.

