### Implementation of the colorectal bundle

In our study protocol we defined three time periods in order to evaluate the effectiveness of our colorectal bundle. We collected data and analyzed the SSI rate from October 2018 till September 2019, before our bundle was implemented. From October 2019 till September 2020, a first set of measures was established. Therefore, this time period is defined as “during implementation”. In January 2021 the full extent of our colorectal bundle was implemented and the time period “after implementation” started for one year.

Following measures were defined based on a current literature review.

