#### Pre-implementation phase (October 2018–September 2019)

During this time period, 137 patients underwent colorectal surgery. Only basic measures for preventing SSI were performed:

Hair was removed in the operating field with a clipper instead of a shaver.Blood glucose was monitored only during the operation.Antibiotic prophylaxis was applied 60 minutes before the operation.The application of an antibiotic prophylaxis was repeated if the operation lasted longer than 4 hours.Measures of warming were only applied during the operation and in the recovery room.Instruments and gloves were changed after finishing the anastomosis.

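### The article gives two incompatible sets of comparator periods, so the pre-implementation SSI rate is 20.3% in one section and 11.9% in the others

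*Protocol article*

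**What the plan says.** Two schemes stand side by side in the Protocol article.

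- **Patient population.** The 2021 patients "will be compared with the data analyzed by Swissnoso (October 2017–September 2018 and October 2018–September 2019"). For the first of these years: "From 2017–2018 153 patients were included and 31 infections were detected". For the second: "From 2018–2019 after partial implementation of the colorectal bundle actions 126 were included and 15 infections occurred". October 2019–September 2020 is not listed as a comparator.
- **Implementation of the colorectal bundle.** "We collected data and analyzed the SSI rate from October 2018 till September 2019, before our bundle was implemented". Then: "From October 2019 till September 2020, a first set of measures was established", which the section treats as the period during implementation. The Abstract and the headings of the two phase subsections use the same dates. October 2017–September 2018 does not appear in this scheme.

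Statistical methods compares the 2021 rate with the pre-implementation and implementation phases, both unadjusted and adjusted for the NNIS risk index, but attaches no dates to either phase. No section gives an SSI count for October 2019–September 2020.

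Two smaller points touch the same periods. For October 2018–September 2019, Patient population counts 126 patients, whereas the pre-implementation subsection says "During this time period, 137 patients underwent colorectal surgery". The Abstract states: "All patients undergoing colorectal surgery between October 2018 and December 2021 will be included in a prospective observational study", while the phase definitions leave out October–December 2020.

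**The concern.** The stated aim is to find out whether the bundle leads to a significant reduction in SSIs, and that is a before-after question. It needs one agreed before period. Here the same twelve months (October 2018–September 2019) are the partly treated period in one section and the untreated baseline in others.

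The two candidate baselines differ by more than 8 percentage points. Under the Patient population scheme, the fall between the two historical years counts towards the bundle. Under the other scheme it lies outside the comparison altogether. Both historical counts are already known, so if the baseline is not fixed before the 2021 data are analysed, the choice can be made, or appear to have been made, after the result is seen.

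**Working it through.** **Inputs** (Protocol article)
- October 2017–September 2018: 31 SSIs in 153 patients (Patient population). The subtypes agree: 5+8+18 = 31.
- October 2018–September 2019: 15 SSIs in 126 patients (Patient population). The subtypes agree: 2+4+9 = 15.
- 2021: about 150 patients expected (Patient population; Statistical methods).
- Interval method: Clopper-Pearson, 95% (Statistical methods).
- Test and level: not stated. A two-sided 5% level and an unadjusted comparison are my assumptions.

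**Step 1: the plan's own figure.** The Clopper-Pearson limits are the 2.5% quantile of Beta(x, n−x+1) and the 97.5% quantile of Beta(x+1, n−x). With n=150 and x=27 (18%) they are 12.2% and 25.1%, a half-width of 6.44 points. This is also the largest half-width over x=0 to 27. The article's limit of 6.5% is reproduced. It concerns the 2021 rate alone, so the comparator conflict does not affect it.

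**Step 2: the two baselines.**

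| Scheme | Earliest comparator | SSI rate | 95% CI |
|---|---|---|---|
| Patient population | Oct 2017–Sep 2018 | 31/153 = 20.3% | 14.2% to 27.5% |
| Abstract and implementation sections | Oct 2018–Sep 2019 | 15/126 = 11.9% | 6.8% to 18.9% |

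Difference: 20.3 − 11.9 = 8.4 points.

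**Step 3: one illustrative 2021 result, 15/150 = 10.0%.** The formula is z = (p1 − p2) / √[p(1−p)(1/n1 + 1/n2)], with p the pooled rate.
- Against 31/153: p = 46/303 = 0.152, standard error 0.0412, z = (0.2026 − 0.1000)/0.0412 = 2.49, p-value 0.013. Fisher: 0.016.
- Against 15/126: p = 30/276 = 0.109, standard error 0.0376, z = (0.1190 − 0.1000)/0.0376 = 0.51, p-value 0.61. Fisher: 0.70.

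**Step 4: the largest 2021 count that shows a significant reduction.**

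| Baseline | Fisher | Uncorrected chi-square |
|---|---|---|
| 31/153 | 17/150 = 11.3% (p=0.041; 18 gives 0.061) | 17/150 (p=0.033; 18 gives 0.051) |
| 15/126 | 7/150 = 4.7% (p=0.043; 8 gives 0.078) | 8/150 = 5.3% (p=0.049) |

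The two baselines therefore disagree for every 2021 count from 8 to 17 by Fisher (5.3% to 11.3%), or from 9 to 17 by chi-square.

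**Step 5: power, treating each baseline rate as the true one.**

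| Assumed true 2021 rate | Power vs 20.3% (n=153) | Power vs 11.9% (n=126) |
|---|---|---|
| 5% | 98% | 55% |
| 6% | 96% | 41% |
| 8% | 87% | 20% |
| 10% | 70% | 7% |

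**The case against.** Four arguments deserve weight.

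1. **A definition does exist.** The Abstract, the implementation section and the two phase subsections agree with each other, so a reader might take Patient population as a slip. I do not think it can be set aside. It is the section that says which historical data the 2021 patients are compared with, and the only one that gives SSI counts for any comparator period. The argument does rule out the stronger reading that the baseline is undefined: two definitions conflict.
2. **The labels are not strictly opposite.** The pre-implementation subsection shows clipper hair removal, antibiotic redosing after four hours and the glove and instrument change already in use, all of which are among the nine actions. Calling that year partly implemented is then loose wording. This softens the conflict of labels but leaves the conflict over comparator years.
3. **Both historical contrasts may be reported.** Statistical methods compares 2021 with both earlier phases, and Patient population lists both 31/153 and 15/126. It would be too much to say that an analyst is free to report only one. What is unsettled is which period is the baseline, and whether 2017–2018 or 2019–2020 belongs in the comparison at all.
4. **The p-values rest on a test that the article does not name**, and an NNIS-adjusted comparison is also planned. This stands as a limit on the exact thresholds. The choice between Fisher and chi-square moves one threshold by a single patient.

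Two further inferences are tempting and not supported. A reader might call 126 versus 137 a contradiction, or compute 15/137. One figure is patients included in the Swissnoso data and the other is patients operated on, so the populations may differ, and no SSI count is given for the 137. A reader might also call the October–December 2020 gap unexplained. The Discussion says the pandemic moved the prospective period from an October 2020 start to January 2021. That accounts for the gap, though not for the Abstract's continuous inclusion window. Nor does it explain the comparator conflict, since it concerns only the prospective period.

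**Conclusion.** The point holds as an internal inconsistency that has to be corrected before analysis. The article carries two incompatible sets of comparator periods, and neither the undated phases in Statistical methods nor the timeline note in the Discussion reconciles them. The pre-implementation rate is 20.3% or 11.9% depending on the section followed. Under an unadjusted two-sided 5% Fisher test with 150 patients in 2021, any count from 8 to 17 SSIs is a significant reduction against one baseline and not against the other.

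These figures assume the test, the level and exactly 150 patients. That the two baselines differ materially does not depend on those assumptions, or on which set of dates proves correct. The documents do not show which set is correct. The 126 versus 137 difference and the Abstract's inclusion window are matters for clarification only.

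**What to change.** Before 2021 outcomes are analysed:

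- Reconcile the Abstract, Patient population, Implementation of the colorectal bundle, the phase subsections and Statistical methods, using the hospital's record of when each measure was introduced.
- Put one table in Methods with, for each phase, its dates, the measures in force, the number of patients and the number of SSIs. Refer to it throughout.
- State in Statistical methods which dated period is the pre-implementation baseline. If October 2019–September 2020 is kept as a phase, supply its counts from existing surveillance records. If October 2017–September 2018 is kept, give it a place in the phase scheme.
- Say whether the 126 and the 137 are different populations, and use the one that matches the denominator in Statistical methods (patients undergoing colorectal surgery). Unless SSIs are counted for the 137, do not report a rate on that denominator, or label it as an assumption.
- Align the Abstract's inclusion window with the October–December 2020 gap left by the pandemic delay.

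The cost is a modest amount of record checking and a text correction. No new patients are needed, but the 2019–2020 counts would have to be retrieved if that phase stays. The possible downside for the sponsor is a less favourable baseline: against 15/126, a significant fall would need about 7 SSIs or fewer in 150, compared with 17 or fewer against 31/153.

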### Inclusion and exclusion criteria

All patients aged 18 years or older undergoing elective or emergency colorectal surgery from January 2021 until December 2021 will be included in the study. Written informed consent will be obtained. Patients under 18 years of age, pregnant patients or patients who refuse or are unable to give informed consent due to mental status, will be excluded from the study.

### Implementation of the colorectal bundle

In our study protocol we defined three time periods in order to evaluate the effectiveness of our colorectal bundle. We collected data and analyzed the SSI rate from October 2018 till September 2019, before our bundle was implemented. From October 2019 till September 2020, a first set of measures was established. Therefore, this time period is defined as “during implementation”. In January 2021 the full extent of our colorectal bundle was implemented and the time period “after implementation” started for one year.

Following measures were defined based on a current literature review.

There are multiple studies assessing the different methods of hair removal prior to surgery [8], such as shaving, clipping and chemical depilation. Compared with shaving, clipping leads to a significant reduction of SSI [9]. During shaving, the skin experiences microscopic cuts which can lead to colonization of microorganisms and thereby increases susceptibility for post-operative wound infections. Therefore, our first action is to remove hair with a clipper.Surgery leads to a release of catabolic hormones as well as decrease in pancreatic beta-cell function, causing stress-induced hyperglycemia. Several studies have shown the association between hyperglycemia and elevated risk for SSI. Close glucose monitoring leads to a reduction of SSI, especially in non-diabetic patients [10]. A risk of hypoglycemia is described, but no serious adverse events occurred during treatment [11]. The second action is therefore the monitoring of blood glucose and the treatment with either insulin or glucose according to our scheme.The application of antibiotics in order to reduce SSI is well established [12]. Studies show that the optimal time window for surgical antimicrobial prophylaxis is 30–59 minutes prior to incision [13]. Accordingly, our third action is to apply an antibiotic prophylaxis within the time frame.Zanetti et al. could demonstrate that the redosing of prophylactic antibiotics during cardiac surgery can significantly reduce SSI [14]. Subsequently, the fourth action is to repeat the intravenous antibiotics if the operation lasts more than four hours.The fifth action focuses on optimal body temperature. Perioperative hypothermia leads to SSI [15,16]. The application of warming systems reduces infections in colorectal surgery [17]. If core temperature is below 35°C, additional warming tools are applied, such as warm intravenous fluid. There is limited data on adverse effects, such as thermal burns.The sixth action includes glove and instrument changes after finishing the anastomosis. Wearing the same gloves over a long period of time may cause microbiological contamination. Hence, in arthroplasty surgery, changing gloves was shown to significantly reduce SSI [18]. A change of instruments prevents a potential bacterial contamination of the abdominal cavity.The seventh action is the use of wound protectors. In laparoscopic as well as in open surgery, dual ring wound protectors lead to a reduction of SSIs [19]. Most likely, a barrier between surgical field and wound can decrease bacterial contamination [20]. Prevention of temperature loss of the wound leads to an improved blood perfusion and reduces SSI.The eight action concerns the surgeons’ experience. Colorectal operations are exclusively performed with the support of a well experienced consultant surgeon.Our ninth and last action focuses on preoperative showering. Torres et al. have shown that a shower, even with customary soap the night before surgery, can significantly reduce SSIs [21].

As previously mentioned, our colorectal bundle was implemented gradually over a time period of three years. In the following, a detailed implementation plan is listed.

#### Pre-implementation phase (October 2018–September 2019)

During this time period, 137 patients underwent colorectal surgery. Only basic measures for preventing SSI were performed:

Hair was removed in the operating field with a clipper instead of a shaver.Blood glucose was monitored only during the operation.Antibiotic prophylaxis was applied 60 minutes before the operation.The application of an antibiotic prophylaxis was repeated if the operation lasted longer than 4 hours.Measures of warming were only applied during the operation and in the recovery room.Instruments and gloves were changed after finishing the anastomosis.

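### The 2018–19 baseline already contained part of the bundle, so comparing 2021 with it estimates an incremental effect, not the effect of the nine-measure bundle

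*Protocol article*

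**What the plan says.** The Background states that "we created a colorectal bundle containing 9 measures", and the Abstract (Discussion) sets the aim as determining "whether the colorectal bundle designed and implemented at Cantonal Hospital Lucerne, will lead to a significant reduction of SSIs". The section on implementation of the bundle numbers the nine actions and defines the baseline: "We collected data and analyzed the SSI rate from October 2018 till September 2019, before our bundle was implemented".

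The Pre-implementation phase section then says of the same twelve months that "Only basic measures for preventing SSI were performed". Its list includes "Hair was removed in the operating field with a clipper instead of a shaver" and "Instruments and gloves were changed after finishing the anastomosis", along with intra-operative glucose monitoring, antibiotic prophylaxis, redosing in long operations, and warming.

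The Patient population section describes 2018–2019 differently: "From 2018–2019 after partial implementation of the colorectal bundle actions 126 were included and 15 infections occurred". It names two comparators for the 2021 cohort, October 2017–September 2018 (31 infections in 153 patients) and October 2018–September 2019. Statistical methods plans to compare the 2021 rate with the pre-implementation and implementation phases, unadjusted and adjusted for the NNIS index, but gives no dates for those phases.

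**The concern.** The aim concerns the bundle as a whole, but the period labelled as its absence already held part of it. Components present in both periods cannot contribute to a difference between them. If 2021 looks no better than 2018–19, a reader guided by the label would conclude that the bundle does not work. If 2021 looks better, the gain would be credited to nine measures when at most the changed ones can have produced it. The article's Discussion treats whether whole bundles work as an open question, so this attribution bears on its main message.

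The period also has two roles. It is the pre-implementation phase in one section and the partly implemented phase in another, so the reader cannot tell which comparison will carry the conclusion.

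**Working it through.** **The plan's own figure.** For 27/150 = 18.0%, the Clopper-Pearson 95% interval is 12.2% to 25.1%, with half-width 6.44%. The stated bound of 6.5% holds. It concerns the precision of a single rate and does not bear on this point.

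**Measures by period**, from the numbered actions and the three phase sections:

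| Action | Oct 2018–Sep 2019 | Oct 2019–Sep 2020 | 2021 |
|---|---|---|---|
| 1 Clipper | in place | – | no change listed |
| 2 Glucose | in part (monitoring during surgery only) | – | intensified |
| 3 Antibiotic prophylaxis | given; stated timing 60 min, against 30–59 min in the action list | – | no change listed |
| 4 Redosing | in place | – | no change listed |
| 5 Warming | in part | – | intensified |
| 6 Gloves and instruments | in place | – | no change listed |
| 7 Wound protector | not listed | new | continues (assumed) |
| 8 Consultant support | not listed | new | continues (assumed) |
| 9 Shower | not listed | not listed | new |

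At baseline, 3 actions are in place as described, 2 are in part and 1 is at a different timing, so 6 of 9 appear in some form. Listed changes up to 2021 are 3 new + 2 intensified = 5 of 9. Three (1, 4, 6) do not change. For action 3 the article states two timings and no change.

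**What the contrast can see.** As an illustration, assume that the whole bundle would halve the risk (relative risk 0.5) and that a share s of that effect, on the log scale, comes from the five changed measures. The contrast then sees a relative risk of 0.5^s. From 15/126 = 11.9%, the expected 2021 rate is 11.9% × 0.5^s:

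- s = 1: relative risk 0.50, rate 6.0%
- s = 0.75: 0.59, 7.1%
- s = 0.5: 0.71, 8.4%
- s = 0.25: 0.84, 10.0%

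The documents give neither the relative risk nor s. A small difference is therefore compatible with an effective bundle.

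**Does the choice of baseline matter?** The rates are 31/153 = 20.3% (2017–18) and 15/126 = 11.9% (2018–19). Take 150 patients in 2021 and an uncorrected chi-square test, z = (p1 − p2) / √[p(1 − p)(1/n1 + 1/n2)] with p the pooled rate. A two-sided 5% level is assumed, since the article states none for the comparison.

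- 17/150 (11.3%) against 31/153: p = 48/303 = 0.158, z = 0.0893/0.0420 = 2.13, p-value 0.033. For 18/150 the p-value is 0.051.
- 9/150 (6.0%) against 15/126: p = 24/276 = 0.087, z = 0.0590/0.0341 = 1.73, p-value 0.083. For 8/150 the p-value is 0.049.

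Every 2021 count from 9 to 17 is thus significant against 2017–18 and not against 2018–19. The lower edge is fragile: with the same 15 infections over 137 patients, 8/150 gives p = 0.080, and Fisher's exact test of 8/150 against 15/126 gives p = 0.078.

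**The case against.** The strongest reply is that nothing is hidden. The article says the bundle came in gradually, itemises each phase, and in Patient population openly calls 2018–2019 partly implemented. Existing practice against the completed bundle is a normal comparison for a quality-improvement project, and the aim as worded does not claim an untreated baseline. Most of this stands. The contents are disclosed and the contrast is informative about the increment. The fault lies in the label and in the conclusion it invites, and disclosure in one section does not remove the contrary statement in another. The limitations say that single measures cannot be separated, but not that the comparator already held part of the bundle.

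Three stronger readings are tempting and should be resisted.

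- A reader might infer that a full six-measure bundle was in place at baseline, or that most of the bundle was identical in both periods. The table does not support this: only three actions match as described, and five of nine change.
- A reader might take the low count needed in 2021 for significance against 15/126 (8/150 or fewer) as evidence of the overlap. That threshold follows from the sample sizes and would be the same if baseline care had contained no bundle measure.
- A reader might point out that 11.9% is already below the 13.7% national average. That average is for October 2016–September 2017 and says nothing about which measures were in use.

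**Conclusion.** The point holds as one of labelling and inference. The statement that October 2018–September 2019 preceded the bundle conflicts with the list of measures for that period and with the Patient population section. Comparing 2021 with it estimates the added effect of three new and two intensified measures over existing practice, subject to before/after confounding. It does not estimate the effect of the nine-measure bundle, and a null result would not show that bundle ineffective. It would go too far to say the comparison shows nothing.

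The practical size is the range of 9 to 17 infections in 150 patients (6.0% to 11.3%), where the significance statement depends on which year serves as baseline. This rests on 150 patients in 2021, the counts in Patient population, an uncorrected chi-square test and an assumed two-sided 5% level. It shows that the choice of baseline is consequential; it does not measure the overlap. Whether 2017–18 was free of actions 1 to 6 cannot be told from the article.

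**What to change.** 1. For 2021 against 2018–19, restate the aim and the permitted conclusion as the incremental effect of the measures added or intensified after September 2019. State that a null result does not speak to the bundle as a whole.
2. Add the baseline overlap to the limitations in the Discussion. A measure-by-period table like the one above would make it visible, though this is optional because the phase sections already hold the content.
3. Reconcile Patient population, Implementation of the colorectal bundle and the Pre-implementation phase section on which period is pre-implementation and on its denominator. The first gives 126 patients included and the last 137 operated on; if both are right, say how they relate and which one the SSI rate uses.
4. Reconcile the prophylaxis timing in the action list with that in the Pre-implementation phase section, and say whether action 3 changed between periods.
5. Rest any whole-bundle claim on the 2017–18 comparison already named in Patient population (31/153), and only to the extent that records show which of actions 1 to 6 were not yet in use then.

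The cost is a narrower claim, some rewording and a check of records on earlier practice. No new patients or outcome data are needed.
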